##### Aerobic-based component

Individuals with bone metastases will be prescribed either stationary cycling, water walking or walking. For individuals without bone metastases, other modes such as conventional cycling, rowing or cross trainers are also prescribed. Equipment accessibility, metastasis location, pain and preference influence what mode is prescribed. For individuals currently completing two sessions or less a week, two sessions a week will be prescribed for the first 3 weeks. If individuals are completing three or more sessions, then they will be prescribed three specific aerobic sessions. Individuals are encouraged to complete extra aerobic sessions if they feel capable. In terms of duration of sessions, participants will complete 2-3 sets of between 6 and 15 min, with rest intervals ranging from 0 to 5 min or 1 session of 30 min with no prescribed rest (Table 4). Session duration and rest intervals will be based on what activity duration the participant feels is feasible, if they are currently meeting this level and an ability score based on previous experience, levels of fatigue and confidence for completing two sessions per week. Intensity will be prescribed using the OMNI aerobic exercise scale of perceived exertion [50]. Intensity will be prescribed individually and will be between six and seven out of ten (moderate intensity) as determined by current fatigue levels and both experience and confidence.

**Table 4 Tab4:** Aerobic training prescription for session duration based on participant self-assessment of exercise duration feasibility, current participation and ability

Duration feasible	Meeting duration	Ability	Aerobic prescription	Total active minutes
0-4 min	No	Low/High^a^-	2 × 3-min efforts with 3-5 min rest	6 min
0-4 min	Yes	Low/High^a^	2 × 4-minute efforts with 3-5 min rest	8 min
5-9 min	No/yes^a^	Low	2 × 5 minutes with 2 min rest	10 min
5-9 min	No/yes^a^	High	3 × 5 minutes with 2 min rest	15 min
10-19 min 10-19 min	No/yes^a^ No	Low High	2 × 10-min efforts with 5-min rest	20 min
10-19 min 20-29 min	Yes No/yes^a^	High Low	2 × 15-min efforts with 5-min rest	30 min
20-29 min 30-44 min 30-44 min 45-59 min 60 min +	No/yes^a^ No Yes No/yes^a^ No/yes^a^	High High Low Low Low	1 × 30-min effort	30 min
30-44 min 45-59 min 45-59 min 60 min +	Yes No Yes No/yes^a^	High High Low High	3 × 10-min high intensity	30 min
Unknown	No/Yes^a^	High/low^a^	2-3 × 5-10 min efforts with 2-5 min rest	10-30 min

^a^Prescription did not differ based on this variable for this prescription

Flexibility exercises will be prescribed based on previous work by Galvão et al. (see Table 2), which has been shown to be safe. Static stretching will involve all major muscle groups involved in the session held for 30-60 s over a period of 2-4 sets and will be prescribed via pictorial and written instructions.

##### Tele-health coaching and monitoring of progress

To keep participants engaged in the programme and ensure sufficient support, participants will also have access to an accredited exercise physiologist (HE). The role of the exercise physiologist will be to encourage uptake of the 8-week individually prescribed programme, provide feedback and monitor progress over the 8-week intervention period. Recent reviews of online digital behaviour change interventions suggest that the inclusion of human support increases the efficacy of online interventions [51]. The exercise physiologist will make contact with participants allocated to the intervention during week one of the programme (by phone or internet call). They will discuss participant goals, provide advice about how best to use the programme to achieve their goals, and offer remote monitoring of participant progress throughout the 8 weeks. Remote monitoring will involve reviewing data entered into the website by participant’s weekly and providing encouragement, feedback and advice based on performance. Contact after week one will occur via email and text messages (up to one per week), with the exception of week three, which will involve a follow-up call (by phone or internet). Participants will have the option of submitting questions to the exercise physiologist whenever they would like to via ‘the ask the EP’ (exercise physiologist) feature of the website. Responses will be sent to participants electronically where possible.

##### Additional components

*Library*. The Exercise Guide library is populated with 25 short articles written in layman’s language about different aspects of living with prostate cancer, exercise and behaviour change. Example topics include ‘Can exercise help your sexual health?’, ‘Sitting too much: What are the real consequences’ and ‘Exercise and depression: 5 tips to move your mood’.

*Diary*. A paper-based exercise diary will be provided to participants in the intervention group to self-report specific aspects of the resistance training (exercises, sets, repetitions, session rate of perceived exertion, duration, bone pain visual analogue score and general pain visual analogue scale), aerobic training (type, duration, session rate of perceived exertion, bone pain visual analogue score and general pain visual analogue scale) and stretching exercise sessions performed. This will allow researchers to monitor and report exercise completed, subjective intensity and any changes in pain levels.

### Waitlist control group

Participants randomised into the wait-list control group will complete the baseline outcome measures as seen in Table 5 and will then be asked to continue with usual care, including maintaining their current physical activity levels for 8 weeks. In week nine, wait-list control participants will repeat the outcome measures. At the end of the intervention, the control group will be sent therabands, given access to the eHealth tool for 8 weeks, complete two tele-coaching sessions and receive weekly contact from an exercise physiologist as authors felt it was unethical to deny participants access to supported treatment.

**Table 5 Tab5:** Overview of measurement tools (page 17)

Outcome	Measure	Number of items	Intervention group	Control group	Collection point (week)
Acceptability	Module ratings	10	✓	x	1-8
	Website perceived personal relevance [52]	3	✓	x	9
	Client Satisfaction Questionnaire [34]	8	✓	x	9
	Perceived Environmental Supportiveness Scale [53]	15	✓	x	9
	Qualitative data (open-ended survey questions and qualitative interview)	4	✓	x	9
Usability	Software usability scale [35]	9	✓	x	9
Usage	Website usage data [54]	3	✓	x	1-8
	Number of exercise sessions	2	✓	x	1-8
Adverse events	Common Terminology Criteria for Adverse Events V.5.0 grading criteria	1	✓	✓	9
Mechanisms of action	Self-efficacy [55]	9	✓	✓	0, 9
	Outcome expectations [55]	8	✓	✓	0, 9
	Motivation type [56]	19	✓	✓	0, 9
	Social Support [55]	2	✓	✓	0, 9
	Intention [57]	4	✓	✓	0, 9
	Behavioural capability [52]	2	✓	✓	0, 9
	Habit formation [43]	4	✓	✓	0, 9
Behaviour change	ActiGraph Accelerometer [54]	1	✓	✓	0, 9
	Modified Godin-Leisure time questionnaire [12]	4	✓	✓	0, 9
	Self-rated exercise adherence [58]	2	✓	x	9
Health outcomes	European Organisation for Research and Treatment of Cancer Quality of Life-Core 30 [59]	30	✓	✓	0, 9
	Functional Assessment of Chronic Illness Therapy-fatigue subscale [60]	13	✓	✓	0, 9
	Hospital Anxiety and Depression Scale [61]	10	✓	✓	0, 9
	The Pittsburgh Sleep Quality Index [62]	14	✓	✓	0, 9
Sub-study physical function	400 m self-paced walk [14]	1	✓	✓	0, 9
	Timed up-and-go test [12]	1	✓	✓	0, 9
	Repeated chair stand [63]	1	✓	✓	0, 9
	One-repetition maximum [14]	2	✓	✓	0, 9

### Measures

#### Feasibility

##### Trial parameters

Screening, recruitment and attrition rates will all be tracked, with reasons for ineligibility, lack of interest and drop-out recorded where possible. Recruitment source will also be assessed during study enrolment. The proportion of participants with complete data for each outcome measure will be assessed, along with the number of reminders and data collection attempts.

##### Intervention parameters

The time taken to deliver coaching sessions and respond to questions asked using the ‘ask and EP feature’ will be recorded in order to provide a proxy indicator of cost of delivery.

#### Success of the intervention

##### Acceptability

The acceptability of the intervention will be assessed using a mixed-methods approach. Participant’s perceptions of module content will be assessed in real-time using a five-star rating system (1—poor to 5—excellent). All other acceptability items will be assessed in week 9. Perceived personal relevance of website content will be assessed via survey using three items designed to evaluate the success of tailoring on a 7-point Likert scale (e.g. ‘the web-based content was written with someone like me in mind’) [52]. The extent to which the coaching was perceived as motivationally supportive will be assessed using the 15-item perceived environmental supportiveness scale [53] and overall satisfaction with the intervention as a health service will be assessed using the client satisfaction Questionnaire-8 [34]. Finally, qualitative data will be collecting using open-ended survey questions and qualitative interviews exploring the pros and cons of the website, any unmet needs, and recommendations for improvement, including any suggested changes to intervention length.

##### Usability

Usability of the intervention website will be assessed using the System Usability Scale [35]. The survey consists of a 9-item questionnaire with five response options for respondents ranging from ‘strongly agree’ to ‘strongly disagree’.

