### Pre-established criteria

Feasibility of conducting a larger-scale evaluation will be interpreted based on the following:
The recruitment goal has been reached (66 participants in 10 months).Behaviour change data are collected for ≥ 75% of participants recruited within the study.Physical functioning data (collected on a subset of participants) can be collected for ≥ 75% of participants that (a) reside within 30 km from a study testing site and (b) are invited to complete testing.

The success of the intervention will be interpreted based on the following:
The acceptability of the intervention is satisfactory (score of ≥ 20 on the client satisfaction questionnaire) [34].The system usability is satisfactory (score of ≥ 68 on the software usability scale) [35].There is no grade 3+/life threatening or severe adverse events attributed to participating in the intervention using the Common Terminology Criteria for Adverse Events V.5.0 grading criteria.There is evidence of meaningful participation in either aerobic activity and or resistance-based activity in the intervention group relative to the wait-list control. As the exercise prescription will be personalised, it is difficult to specify an average cut-point; however, we anticipate a between-group difference of at least 30 min of aerobic activity and/or one session of resistance training. This would be indicative of behaviour change that is in line with the minimum level of exercise progression prescribed in our intervention and should also allow us to detect differences in maintenance of activity (equivalent to one session per week) amongst those that enter the study already completing some exercise.

The trial team will determine if progression to a larger scale evaluation is warranted based on the criteria and will work together to revise aspects of the protocol if problem areas are identified (e.g. if recruitment is slow the study may still progress if additional recruitment sites can be secured). The process evaluation will be used to inform improvements to the intervention if usability, acceptability or potential for efficacy issues are identified.

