##### Health outcomes

All health-related outcomes will be assessed at baseline and immediately post-intervention. Health-related quality of life will be assessed using the EORTC Quality of Life-Core 30 (EORTC QLQ-C30), which is a validated and reliable questionnaire for quality of life in cancer patients [65]. The 30-item core survey assesses a comprehensive range of quality of life domains including functioning (physical, role, cognitive, emotional and social), symptoms (fatigue, nausea and vomiting, sleep, pain, appetite, shortness of breath), financial hardship and global health status [59].

The 13-item Functional Assessment of Chronic Illness Therapy-fatigue subscale will be administered to measure participant’s level of fatigue. The questionnaire has been demonstrated as a valid and reliable measure [60]. The Hospital Anxiety and Depression Scale will be used to evaluate changes in anxiety and depression by using two 7-item Depression and Anxiety sub-scales [61]. The reliability and validity has been shown to be acceptable in individuals with prostate cancer [66]. Additionally, the Pittsburgh Sleep Quality Index questionnaire will measure sleep quality. Psychometric evaluation of the Pittsburgh Sleep Quality Index in cancer patients has established internal consistency, reliability and construct validity [62].

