#### Intervention mechanisms

The proposed behavioural change mechanisms will be assessed at baseline and week 9. This will include measuring barrier self-efficacy for resistance and aerobic activities (9 items [55]), outcome expectations (8 items [67]), motivation type (19 items [56]). Social support (2 items [55]), intentions (4 items [57]), behavioural capability (7 items [52] and habit formation (4 items [43]). Collection of this data will provide preliminary insight into if the intervention is working as expected and will also provide useful information for directing further tailoring efforts (e.g. by allowing us to examine how variable individuals are in these variables at baseline, and thus the extent of tailoring that is needed). Collection of this information will also be useful for establishing feasibility of collecting data needed for a formal mediation analysis in the main trial.

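### The usability success threshold of 68 lies outside the raw score range of the nine-item survey described, and no rescaling is fixed, so an unstated scoring choice can decide whether the criterion is met

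*Protocol article*

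**What the plan says.** Pre-established criteria lists four conditions for judging the success of the intervention. One reads: "The system usability is satisfactory (score of ≥ 68 on the software usability scale". No score range, item coding or multiplier is given there.

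The Usability section calls the instrument with the same reference number the System Usability Scale and describes it thus: "The survey consists of a 9-item questionnaire with five response options for respondents". Table 5 also gives nine items, under the name software usability scale. The usability item count is therefore consistent; the instrument's name is not.

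Two other entries in Table 5 disagree with the text:

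- **Hospital Anxiety and Depression Scale.** Table 5 lists 10 items. The Health outcomes section refers to "two 7-item Depression and Anxiety sub-scales".
- **Behavioural capability.** Table 5 lists 2 items. The Intervention mechanisms section gives 7 items under the same reference.

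**The concern.** The threshold and the survey are both fixed in the article, but they do not fit each other as printed: no sum of nine five-option items reaches 68. Some rescaling must therefore be intended, and more than one is plausible. If it is chosen after the responses have been seen, the criterion is no longer pre-specified. The introduction gives transparency about those criteria as a reason for publishing the protocol, and the criteria inform the decision on a larger evaluation.

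The item-count mismatches have a different consequence. If the online questionnaire was built from Table 5, the anxiety and depression subscales could not be scored as the text describes.

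**Working it through.** **Inputs from the article.** Threshold: at least 68 (Pre-established criteria). Items: 9 (Usability; Table 5). Response options: 5 (Usability).

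**Assumptions, not in the article.** Items are coded 0-4 or 1-5. The 0-4 sum is rescaled either by 2.5, a multiplier that would bring ten such items to 10 × 4 × 2.5 = 100, or by 100/36, which stretches nine items to the full 0-100 range. The threshold has no stated derivation, so there is no figure of the plan's own to reproduce.

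**Step 1: raw range.** Coded 0-4, the maximum is 9 × 4 = 36. Coded 1-5, it is 9 × 5 = 45. Both are below 68.

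**Step 2: what 68 requires under each rescaling of the 0-4 sum.**

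| | × 2.5 | × 100/36 |
|---|---|---|
| Maximum score | 36 × 2.5 = 90 | 36 × 100/36 = 100 |
| Raw sum equal to 68 | 68 / 2.5 = 27.2 | 68 × 36/100 = 24.48 |
| Share of the maximum | 27.2 / 36 = 75.6% | 24.48 / 36 = 68% |
| Mean item score (0-4) | 27.2 / 9 = 3.02 | 24.48 / 9 = 2.72 |
| First whole raw sum that meets 68 | 28, scoring 70 | 25, scoring 69.4 |

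**Step 3: where the two rules disagree.** A mean raw sum from 24.48 to just under 27.2 fails under × 2.5 and passes under × 100/36. On the 0-100 basis, the × 2.5 rule puts the bar at 27.2 × 100/36 = 75.6, which is 7.6 points higher. To illustrate, an average equal to the second-best answer on every item gives 9 × 3 = 27. That scores 67.5 under × 2.5 and 75 under × 100/36.

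**Step 4: item counts.** For the Hospital Anxiety and Depression Scale, two subscales of 7 make 14 items, against 10 in Table 5, a difference of 4. For behavioural capability, the text has 7 and Table 5 has 2. Table 5 agrees with the text for self-efficacy (9), outcome expectations (8), motivation type (19), social support (2), intention (4), habit formation (4), the quality-of-life core questionnaire (30), the fatigue subscale (13) and the supportiveness scale (15). A different counting convention is therefore an unlikely explanation for the two mismatches.

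**The case against.** The strongest reply is that scoring rules are normally left to the cited instrument, the full protocol or the analysis plan. The article prints no scoring formula for its other questionnaires either, including the client satisfaction questionnaire with its own cut-off of 20. For those instruments the reply stands, and their silence is no finding. Usability differs because the article prints a threshold together with an item count and a number of options that cannot produce it without a rescaling.

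A reader might infer that 68 cannot be applied at all, or that it is too strict. The article supports neither. A ceiling of 90 still leaves 68 reachable, and both rules reach it. Calling the bar too strict would require knowing that × 2.5 will be used and which form 68 was set for. The article says neither, and if the nine items are stretched to 0-100, 68 keeps its meaning as 68% of the maximum.

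Two further points are fair. The criterion judges the intervention, and no participant-level pass rule is stated, so an example about one respondent is only illustrative; this is why Step 3 uses means. Missing 68 also does not stop the programme, because the trial team decides on progression and may revise the intervention.

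The Table 5 mismatches feed no success criterion. Nothing shows that the fielded survey follows the table.

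**Conclusion.** The point holds as an ambiguity in a pre-specified success criterion. That the raw maximum (36 or 45) lies below 68 follows from the article alone, given consecutive integer coding. The size of the ambiguity rests on the assumed pair of rescalings and on reading the criterion as a group mean: 68 stands for either 68% or 75.6% of the attainable score, and verdicts reverse for mean raw sums from 24.48 to just under 27.2 out of 36. Whether the trial's mean will fall in that band cannot be known from the article.

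It is a moderate point. It affects one of four success conditions in a pilot whose team keeps discretion over progression. It is still worth settling, because the remedy is cheap and loses its value once responses have been seen.

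The Table 5 contradictions are real but secondary. They become substantive only if the survey was built from the table, in which case 4 of the 14 anxiety and depression items would be missing.

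**What to change.** Before any usability data are analysed, do one of the following:

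- State beside the criterion that the nine items are coded 0-4, that the sum is multiplied by 100/36 to give a 0-100 score, and that the group mean is compared with 68. The team should confirm that its 68 benchmark refers to a 0-100 scale.
- Field the complete form to which the 68 benchmark refers, and score it by that form's own rule. Recruitment began in February 2020, so this route is clean only if no participant has yet answered the nine-item version.

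Use one name for the instrument in Pre-established criteria, Table 5 and the Usability section.

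Separately, check the online survey against the text for the Hospital Anxiety and Depression Scale and for behavioural capability, then correct Table 5 or the text so that both match what is fielded.

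The first route costs one scoring sentence and a check of the survey build, with no change to design or sample size. The second adds the items needed to complete the form.

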##### Usage

Website usage data, including the number of logins, time on site and number of modules completed, will be assessed using Google analytics and inbuilt website tracking software [54]. Usage of the exercise diary will also be recorded in terms of number of sessions logged.

##### Adverse events

Participants will be advised to report any injuries either through the website or by calling the study project coordinator (HE). An item on adverse events will also be included in the follow-up questionnaire based on the Common Terminology Criteria for Adverse Events V.5.0 grading criteria.

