**Fig. 2 Fig2:**
[figure not shown]
Study flow diagram

To be eligible, participants must have been diagnosed with metastatic prostate cancer (as confirmed by their physician) and have medical clearance from their physician (General Practitioner, Medical Oncologist, Radiation Oncologist or Urologist). Physicians are required to provide details regarding the extent and location of metastases. Participants also need to have access to a computer with the internet, be able to read and write in English and provide written consent prior to baseline testing. Finally, to be eligible participants should not already engage in two sessions of resistance-training and 60 minutes of structured moderate-vigorous aerobic exercise per week. Participants meeting one target but not the other will be eligible.

Patients will be deemed ineligible if they have any absolute contraindications to performing moderate physical activity (resistance, aerobic and flexibility) for at least 20 min (in bouts of 5 min), up to 2 days of the week. This includes no recent serious cardiovascular events (within 12 months), unstable bone metastases, spinal compressions or acute illness and infection [36]. Participants will also be excluded from the study if they have moderate to severe bone pain (Common Terminology Criteria for Adverse Events V.5.0 grading criteria).

Participant retention strategies will include flexible scheduling for telehealth consultations, reminder calls/texts and consistent study staff. Criteria for discontinuing intervention include participant request and worsening conditions which are absolute contraindications to exercise (including unstable bone metastasis, spinal compression and significant cardiovascular events). Concomitant care will be permitted during the study and any changes in treatment will be recorded.

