### Data management and monitoring

All research data will be stored on a password-protected network drive on a password-protected computer and only members of the study team will have access to this data. Questionnaire data will be recorded using a secure online data collection instrument (RedCap) with participants being sent web links at the appropriate time points. Participant contact information and name will be held in a separate file to study data, and unique ID numbers will be allocated. Only ID numbers will appear alongside outcome data. A trial steering committee (CES, DG, GK, NB) will oversee the trial. Any adverse events will be reported to the committee and the steering committee have the power the terminate the study if necessary. As a clinical oncologist and urologist sit on the trial steering committee, it was determined that a trial data monitoring committee was not required. Trial results will be submitted for publication and communicated in a relevant medical or scientific journal.

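### Participants are advised to report only injuries as they occur, which is narrower than the adverse events on which safety is judged and which the steering committee oversees

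*Protocol article*

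**What the plan says.** The Adverse events section under Measures gives two routes by which events become known. The first is spontaneous: "Participants will be advised to report any injuries either through the website or by calling the study project coordinator". The second is a question at follow-up: "An item on adverse events will also be included in the follow-up questionnaire". Table 5 lists the adverse-event measure as one item, graded by the "Common Terminology Criteria for Adverse Events V.5.0 grading criteria", in both arms, with week 9 as its only collection point.

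Three other places depend on what these routes bring in:

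- Pre-established criteria: the intervention succeeds on safety only if there are no grade 3 or higher, "life threatening or severe adverse events attributed to participating in the intervention". The abstract lists safety as part of the primary outcome.
- Data management and monitoring: "Any adverse events will be reported to the committee and the steering committee have the power the terminate the study if necessary".
- Participants and screening: grounds for stopping the intervention include "worsening conditions which are absolute contraindications to exercise (including unstable bone metastasis, spinal compression and significant cardiovascular events").

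On contact during the programme, the Tele-health coaching section provides a call in week 1, and then: "Contact after week one will occur via email and text messages (up to one per week), with the exception of week three". It adds: "Remote monitoring will involve reviewing data entered into the website". That review is weekly.

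**The concern.** The reporting advice uses a narrower word than the criterion and the oversight it feeds. A man with chest pain, new leg weakness or growing bone pain may see a symptom of his disease or his age, not an injury. The advice as written does not ask him to report it while he is still exercising.

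The first thing at stake is time. The rule for stopping the intervention works only if the team hears of the condition when it arises, and the committee, which includes clinicians, can act only on what reaches it. The second is completeness. Someone who has such an event and then drops out, or leaves the week-9 questionnaire unanswered, may never enter the safety count.

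**Working it through.** This is a question of scope and timing, so the check sets the protocol's sections side by side.

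**1. Scope of each statement**

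- Advice to participants (Adverse events): injuries.
- Success criterion (Pre-established criteria): adverse events that are severe and attributed to the intervention, not limited to injuries.
- Committee remit (Data management and monitoring): any adverse event.
- Stopping grounds (Participants and screening): unstable bone metastasis, spinal compression, significant cardiovascular events.

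The stopping conditions fall within the criterion's and the committee's term, but not naturally within the participant's. A pathological fracture, which the Introduction mentions, might well be called an injury, so the gap does not extend to it. Nowhere does the article tell participants to report the other conditions when they occur.

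**2. Timing of systematic collection**

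The programme runs for weeks 1 to 8 and the adverse-event item is at week 9. Scheduled calls fall in weeks 1 and 3. Weeks 4 to 8, that is 8 − 3 = 5 of the 8 weeks, have no scheduled call. These are also the weeks in which the exercise prescription may progress (Table 1, Table 3).

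**3. Other routes in the intervention arm**

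- Weekly review of website entries: its stated purpose is encouragement, feedback and advice. The tracker in Table 1 holds overall pain, fatigue and mood, with no cardiac or neurological question.
- The 'ask the EP' feature: available at any time, but it relies on the participant to raise the matter.
- Questions repeated for weeks 4 to 8, and movement-pain questions (Table 1; Web-based exercise prescription): the answers change the prescription. They are not described as producing a report.
- Exercise diary: bone-pain and general-pain scores for resistance and aerobic sessions, but on paper and with no return date stated.
- Recorded treatment changes, and drop-out reasons where these can be obtained.

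Each may bring an event to light, but none is described as adverse-event collection. For controls, the article states no contact between baseline and week 9.

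**4. The protocol's own figure**

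The Sample size section claims that the sample can reveal problems with a probability of 10% or more at 95% confidence. The smallest n with 1 − 0.9^n ≥ 0.95 is ln(0.05)/ln(0.9) = 28.4, so 29. With 33 per arm the claim reproduces, and the reporting wording does not change it.

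**The case against.** The strongest reply is that this is one sentence in a condensed article. The words participants actually receive are in the information sheet and in the website's safety module, neither of which is shown, and either may be wider. That is fair as a limit on what can be concluded about practice. It does not remove the point, because the article does state the trigger and states it narrowly. If the unseen texts are wider, the same edit brings the article into line with them.

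A second reply is that the two routes complement each other. The week-9 item covers all adverse events in both arms, so for anyone who answers it the wording affects when the event is known, not whether it is counted. This stands, and it is why delay is the main risk.

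A third reply is that the criterion counts only events attributed to the intervention, so a spinal compression caused by disease progression alone would not count. This also stands and narrows the effect on the criterion. An exercise-related cardiac event could still fall in the gap, and attribution can be judged only for events that are known.

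A fourth reply is that non-response is already addressed: reminders and flexible scheduling are planned, collection attempts are tracked, and intervention participants are interviewed afterwards. These measures reduce the loss but do not rule it out.

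Two stronger readings are tempting. A reader might infer that a week-1 event would stay unknown for about eight weeks. In the intervention arm that passes over the week-3 call, the weekly review, the messages and the repeated questions. A reader might also infer that the sample can no longer detect safety problems as claimed. The documents give no basis for how many participants would be missed, so no loss of detection can be calculated.

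**Conclusion.** The point holds as a mismatch of scope with a practical consequence. The advice on prompt reporting is narrower than the events on which safety is judged and overseen, and it does not naturally cover the conditions that should stop the intervention. The main consequence is possible late notice of serious non-injury events while exercise continues, most plausibly in the five weeks without a scheduled call. The secondary consequence is possible loss of such events among those who drop out or do not answer at week 9.

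The size cannot be put as a number of participants or events, and no figure in the Sample size section is affected. The conclusion assumes that participants read 'injuries' in its ordinary sense and that the unseen participant materials do not ask for more. If they do ask for more, what remains is an inaccurate description in the article. The change should be made, but the design does not depend on it.

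**What to change.** In the Adverse events section and in the matching advice to participants in both arms, replace the reference to injuries with any adverse event or any new or worsening symptom, whether or not exercise seems to be the cause. Give examples in lay words: worsening bone pain, new weakness or numbness in the legs, loss of bladder or bowel control, chest pain. The existing reporting routes (website or telephone) can stay as they are.

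The cost is a small amendment, which needs steering committee and ethics approval under Protocol changes. The coordinator will also have more reports to review, many of them unrelated to exercise.
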